### Data protection

All data collected in these studies will be maintained and stored in accordance with the data protection regulations. All patient identifiable information (i.e. name, contact details, date of birth, home and work postcode) will be stored in a database separate from the database that holds anthropometric measures, results of blood tests, physiological measures and travel and PA data. Personal data stored on NHS, university or Life Cycle computers will be password protected, and only the study investigators or Life Cycle project administrator will have access to the passwords. Personal data on paper files will be stored in a locked filing cabinet within the School of Policy Studies at the University of Bristol or at Life Cycle. All paper files from Life Cycle will be transferred to the University of Bristol. Data will be stored for 15 years.

### Eligibility

The eligibility criteria for the two pilot RCTs are outlined in Table 2.

**Table 2 Tab2:** Eligibility criteria for the two pilot RCTs

	**Inclusion criteria**	**Exclusion criteria**
CRANK-P	1. Men with D’Amico high-risk localised PCa (*PSA* > 20) or clinical stage ≥ cT2c or Gleason 8/9/10 [59] OR men with any N1 PCa OR men with metastatic PCa (stage M1) 2. Aged 18 years or over 3. Cleared for engaging in PA by the treating consultant	1. Engage in ≥ 150 min of MVPA per week as assessed by the Get Active Questionnaire [60] 2. Uncontrolled hypertension (systolic BP > 160 mmHg and/or diastolic BP > 90 mmHg), for which the individual is not taking medication 3. Comorbidities including myocardial infarction or stroke within the past 6 months or evidence of end-stage renal failure or liver disease, uncontrolled congestive heart failure or angina 4. Use of a mobility aid preventing cycling 5. No previous experience riding a bicycle 6. Any other contra-indications to exercise 7. Are unable to read and communicate in English
CRANK-B	1. Women or men with early BC (i.e. stages 1 or 2) who have completed their primary BC treatment (i.e. surgery, systemic therapy and/or radiation therapy) 2. Aged 18 years or over 3. Cleared for engaging in PA by the treating surgeon	1. Engage in ≥ 150 min of MVPA per week as assessed by the Get Active Questionnaire [60] 2. Individuals with metastatic disease 3. Uncontrolled hypertension (systolic BP > 160 mmHg and/or diastolic BP > 90 mmHg), for which the individual is not taking medication 4. Comorbidities including myocardial infarction or stroke within the past 6 months or evidence of end-stage renal failure or liver disease, uncontrolled congestive heart failure or angina 5. Use of a mobility aid preventing cycling 6. No previous experience riding a bicycle 7. Any other contra-indications to exercise 8. Are unable to read and communicate in English

*BC* breast cancer, *BP* blood pressure, *cT* clinical T category, *N* degree to which cancer has spread to lymph nodes, *M* degree to which cancer has spread to other areas of the body, *MVPA* moderate-to-vigorous physical activity, *NICE* National Institute of Health and Care Excellence, *PA* physical activity, *PCa* prostate cancer, *PSA* prostate-specific antigen

### Sample size

The study will aim to recruit and randomise 40 individuals for each pilot RCT. This sample size is based on recommendations for pilot studies which aim to provide an estimation of a standard deviation for use in the sample size calculation to inform a larger randomised controlled trial [61, 62], as well as the availability of e-bikes. There are no explicit targets regarding the number of individuals to be recruited or screened as we are investigating the feasibility of recruitment from the clinical setting. Based on recruitment rates in a similar population (individuals recovering from colorectal cancer) and recruitment occurring in a clinical setting, we anticipate a recruitment rate of approximately 20% [63]. Recruitment and screening will close when 20 participants have been randomised to each of the two study arms. Based on a previous pilot randomised controlled trial of e-cycling among individuals with type 2 diabetes mellitus, a retention rate of approximately 80% is anticipated [58].

### Consent

Once participants have been identified as eligible to participate in the studies, they will be booked in for a baseline data collection visit (T0). At this visit, a member of the research team will outline the study procedures, as per the information sheet. Participants will be advised that the study is voluntary, and that they have the right to withdraw at any time, without the need for explanation. After this, individuals who wish to participate will be asked to read, complete and sign a consent form, which will be countersigned by the member of the research team obtaining consent.

### Allocation, randomisation and blinding

Randomisation will occur after consent is obtained and baseline data (T0) has been collected. For each pilot RCT, 40 individuals will be randomly assigned to either the e-cycling intervention or waitlist control in a 1:1 allocation ratio. For CRANK-P, individuals will be stratified based on cancer treatment received prior to randomisation. For CRANK-B, individuals will be stratified based on stage of cancer treatment prior to randomisation. Permuted blocks of random size will be used. A random allocation sequence will be generated by an independent statistician using R v4.1.2, package blockrand (v1.5). The randomisation sequence will be accessible through a password-protected Excel file. The researcher will access the Excel file and allocate the participant to either condition in the order issued in the sequence. Researchers will be aware of the group allocation. Participants will be informed of the group allocation via telephone by a member of the research team. Blinding of intervention allocation will not be possible for any participant involved in the trial or the researchers.

### Intervention and control groups

#### Intervention development and content

The development and content of the intervention is being prepared for publication ([name] et al., The development of a theory and evidence-based intervention to increase physical activity in individuals with prostate cancer and breast cancer, the CRANK trials. Manuscript in preparation). Briefly, the intervention was developed in accordance with the MRC guidance for the development of complex interventions [64] and the Behaviour Change Wheel [65]. A programme theory, identifying the theoretical underpinnings of the intervention was developed using theory, evidence and patient and public involvement (PPI). After identifying the hypothesised mechanisms of change, intervention content was guided by the selection of specific behaviour change techniques (BCTs) using the 93-item behaviour change technique taxonomy (BCTTv1) [66]. A total of twenty-three BCTs were identified for inclusion.

The mode of intervention delivery was based on previous feasibility work examining the feasibility of an e-cycling intervention in adults with type 2 diabetes mellitus delivered by the same community organisation [67]. Once developed, the proposed intervention was presented to members of the PPI group consisting of cycling instructors, cancer patients and experts in PA behaviour change. Feedback was elicited through open discussion and in written form. Intervention content, including instructor manuals and participant workbooks, were adapted accordingly. The final intervention content and delivery modes are presented in Additional file 2 and described below.

#### Instructor training

The intervention will be delivered by a Bristol-based charity who specialise in bicycle training, Life Cycle. Instructors are fully qualified National Standard cycle instructors, and so training, provided prior to delivery, will focus on the behavioural aspects of the intervention content. Training will consist of two sessions. Training session 1 (3 h) will provide information on importance of PA for individuals with cancer and the general physical and mental health benefits of engaging in PA. Motivational interviewing techniques will be taught to help instructors engage with participants, and information on the specific content of the intervention will be provided. The use of motivational interviewing has been found to support physical activity behaviour change in cancer patients [68, 69]. Training session 2 (4 h) will provide an opportunity to review the intervention content. Role-playing activities will be conducted and feedback provided from the researchers. Attendance at the training is mandatory for delivering the intervention. Instructors will be observed during initial intervention delivery sessions, and feedback will be provided by the research team. A bi-monthly peer support group will be run enabling instructors to share their experiences of delivering the intervention.

#### E-bike training

Following baseline measures (T0), participants allocated to the intervention will complete e-bike training at Life Cycle. Training will consist of two one-to-one sessions. Training session 1 will be mandatory and will follow the bikeability guidelines for levels 1 and 2. Individuals’ previous cycling experience will be considered when conducting the cycling-specific training. Training session 2 will occur within 2 weeks of session 1. The instructor and participant will discuss the need and/or desire for session 2. Session 2 will provide participants with an opportunity to practice e-cycling skills with the instructor. Training sessions 1 and 2 will last approximately 2 h each. All participants must have completed bikeability level 2 prior to taking the e-bike home.

Throughout these sessions, the instructors will deliver evidence-based behaviour change techniques through motivational interviewing informed conversations. Participants will be provided with a workbook to record notes from discussions with instructors and their e-cycling goals throughout the intervention.

Participants will be encouraged to monitor their e-cycling using either a GPS watch (Fitbit Charge 5) or a paper logbook for the duration of the intervention. If using the GPS watch, participants will have the option to pair the watch with a mobile application to monitor their e-cycling.

Participants will be invited to join a private social media group, one group for each pilot RCT, to share their experiences and ride ideas with other individuals participating in the intervention. At the end of the e-bike training, the participant will be free to take the e-bike home and use as they wish. E-bikes can be ridden home or bike transportation provided by Life Cycle. Upon taking the e-bike home, participants will be provided with maps of cycle routes in the area, instructions of a call out maintenance service in case of breakdown, helmet, pannier, bike lock and lights.

#### E-bike loan

Participants will be loaned the e-bike for 12 weeks for their personal use. Participants will be instructed to use the e-bike as they desire, with no specific daily or weekly cycling frequency or distance targets imposed by the researchers. Throughout the loan period, participants will be invited to attend both study-specific e-cycling group rides run bi-monthly and pre-existing group rides run monthly by Life Cycle. At weeks 4 and 8 of the loan, participants will participate in one-to-one refresher sessions with their instructor (sessions 3 and 4). These sessions will take place at a location of the participant’s choice and last approximately 2 h each. The content of the session will depend on the participant’s needs but will include a review of participants e-cycling progress so far, action planning and goal setting for future riding and practicing riding on established or new routes. At the end of week 12, participants will return the e-bike to Life Cycle, or an instructor will collect the e-bike.

#### 3-month follow-up

Following completion of the intervention, individuals in the e-bike condition will be provided with information, in the form of a booklet, on how to access community-based e-cycling initiatives. This will include how to access the cycle2work scheme, information on community e-bike trial sessions, community e-bike loan availability and e-bike discounts. In addition, a pool of five e-bikes for each trial will be available for participants to loan for 12 weeks from the University of Bristol. These e-bikes will be allocated on a first come, first served basis. Individuals’ decision to seek out e-cycling opportunities at this time will be at their own discretion. Exploring the current available pathways through which individuals can access an e-bike in the community is important for exploring future programme sustainability. Throughout this time, individuals in the e-bike condition will be asked to record any e-cycling activity using the GPS watch and paper logbook.

#### Control group

Individuals assigned to the waitlist control after baseline data collection (T0) will receive two phone calls from the researcher at approximately weeks 4 and 8 to maintain engagement in the study. During these phone calls, the researcher will ask participants about how their cancer treatment is going and will direct participants to cancer support groups in line with standard care procedures. Between post-intervention data collection (T1) and 3-month follow-up data collection (T2), individuals will not be contacted. After the 3-month follow-up, individuals in the control condition will be offered training session 1 and loaned an e-bike for 3 months. Sessions 2, 3 and 4 will not be conducted. Participants will be asked to report any contact they have with other individuals in the study to ensure no contamination between conditions has occurred.

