##### Travel behaviour (changes in transportation modes and trip purpose)

Spatial location data will be collected using a personal GPS receiver (Qstarz International Co. Ltd., Taiwan) to describe participants travel behaviour at baseline (i.e. before obtaining the e-bike), in the final week of the intervention and in the final week of the 3-month follow-up. Participants will be asked to wear the GPS during waking hours and recharge it at night. The device can be worn around the waist or in a pocket as desired. GPS time and positional data will be used to identify journey start and finish times and estimate velocities. In addition, participants will also be asked to complete a 7-day travel diary over the same period as GPS monitoring. The travel diary is adapted from Neves and Brand [100] and will ask participants to record every journey made over the 7-day period. Participants will be asked to classify the journey under one of five categories: commuting for work, commuting for education, travel for business, shopping or personal business and social visits or leisure activities. For each journey, participants will be asked to report the travel mode, start and end time and start and end location. The information from the travel diary will be used to (a) capture contextual data related to trips (e.g. trip purpose), (b) validate the GPS and (c) provide an alternative source of data in case the GPS fails, is not turned on, or the battery dies. This information will allow us to determine the total distance travelled by active transportation (i.e. walking or cycling) compared with motorised transportation and to compare different modes of active transportation.

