##### E-cycling behaviour and intensity

E-cycling behaviour will be measured during the intervention and follow-up period in the intervention group using a Fitbit Charge 5 watch. The Fitbit Charge 5 is an integrated GPS and heart rate monitoring watch which can store up to 7 days of activity tracking. Participants will have the option to pair the device with a smart phone using Bluetooth. If Bluetooth pairing is used, then activity data will be automatically uploaded to the Fitbit website. If the participant chooses not to pair the device, then the data will be downloaded each week by the researcher. The watch will need charging during the loan period; all charging cables and instructions will be provided. Outcomes derived from the watch will include the frequency and duration of e-cycling journeys and intensity of activity associated with e-cycling based on heart rate data. Wrist-worn consumer devices, including the Fitbit, have been reported to have acceptable accuracy for the measurement of heart rate in research settings and are more ecologically valid than research devices [101, 102]. Average journey speed will also be derived. The purpose of journeys will be derived through land use maps and using home and work postcodes. Participants will be provided with a paper logbook should they not wish to use the watch. The logbook will ask participants to record each e-cycling trip, the duration, the start and end location and the purpose. An inbuilt odometer on each bike will also collect data on the total number of kilometres ridden during the trial in case the watch or logbook is not used. Participants will use the watch or complete the logbook for the intervention period and for the 3-month follow-up period. After this time, the watches will be returned to the researcher, and data from the Fitbit device and/or online website will be downloaded to a University of Bristol computer and securely stored. After all data is downloaded, it will be deleted from the Fitbit website and the device itself. Participants will not be required to enter their name, address or email when setting up the Fitbit device; all devices will be connected to a University of Bristol email address, and the participant’s ID will be used in place of their name. However, due to the nature of GPS tracking, participant’s start and end points of journeys will be identifiable from the GPS tracks. This will be made clear to the participants in the information sheet and in the consent form.

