### Data analysis

#### Quantitative analysis

The primary outcomes of this pilot trial include recruitment and consent rates, retention and adherence to study procedures and data provision. Analysis of these data will be descriptive, expressed as frequencies and percentages. Any adverse events will be described appropriately. Characteristics of the sample will be summarised using descriptive statistics (means and standard deviations, medians and interquartile ranges or frequencies and percentages as appropriate). Descriptive comparisons of these data will be made between the intervention and the waitlist control. Evidence of promise of the intervention (i.e. whether the intervention can lead to changes in outcomes measures) will be examined using comparison of change scores between conditions for all outcome measures (except e-cycling during the intervention). See Table 3 for a description of the outcome measures and proposed analysis plan for each outcome. Effect estimates will be presented with 95% confidence intervals reported; *p*-values will not be considered as the study is not powered to detect effectiveness. All analysis will be undertaken in Stata v17.

**Table 3 Tab3:** List of CRANK research questions, associated outcomes, data collection tools, time point measurements and analysis plan

Research question	Outcome	Data collection method/tool	Time point of measurement				Analysis plan
			Baseline (T0)	During intervention	Post (T1)	3-month FU (T2)	
1. Can individuals with prostate/breast cancer be recruited into an e-cycling trial?	• No. of individuals in clinic; no. of meeting eligibility criteria; no. of express interest in participating • Reasons for not wanting to participate in the study • No. of individuals that consent to be part of the study	Study records	X				Frequencies and percentages
2. Are participants’ willing to be randomised, do they remain in the study and adhere to the intervention and data collection methods and what are the rates of harmful events?	• No. of participants retained in study following randomisation • No. of individuals that complete follow-up testing • No. of participants that attend each of the intervention sessions and data collection sessions • No. of harmful events	Study records		X			Frequencies and percentages

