3. Can the intervention be implemented as intended?	• No. of training sessions attended by participants and additional contact with instructors • Extent to which intervention content is completed as planned • No. of and extent of adaptations	Intervention checklists		X			Frequencies and percentages
4. Are the intervention and study procedures acceptable to participants, instructors and clinical team?	• Acceptability of recruitment strategy to clinical team • Acceptability of intervention to participants • Acceptability of study procedures to participants • Acceptability of intervention delivery to instructors	Semi-structured interviews			X		Thematic analysis based on research question
5. What are participants experiences of e-cycling?	• Experiences of e-cycling • Participant’s barriers and facilitators to e-cycling	Semi-structured interviews			X		Thematic analysis based on research question
6. What is the potential effect of the intervention on a range of individual health and behavioural outcomes?	• Weight, BMI and waist circumference	Tanita digital scales, SECA 700, non-stretch take	X		X	X	Comparison of change scores between conditions Reporting of effect estimates with 95% CI
	• Metabolic markers (fasting glucose, insulin, insulin resistance, lipid profile, IGF-I, IGF-II, IGFBP-2, IGFBP-3, PSA^a^)	8-mL blood sample	X		X		
	• General health-related quality of life	EuroQol-5 dimension-5 level	X		X	X	
	• Cancer-specific quality of life	EORTC QLQ-C30 EORTC PR-25^a^ EORTC BR-45^b^	X		X	X	
	• Urinary health^a^	ICIQ-MLUTS	X		X	X	
	• Erectile dysfunction^a^	International Index of Erectile Function	X		X	X	
	• Fatigue	FACIT-F	X		X	X	
	• Self-efficacy for coping with cancer	Cancer Behaviour Inventory — Brief	X		X	X	
	• Cardiorespiratory fitness	Maximum oxygen uptake using cycle ergometer	X		X	X	
	• Hand grip strength	Hydraulic hand dynamometer	X		X	X	
	• Total physical activity (time spent in moderate-to-vigorous physical activity)	Axivity AX3	X		X	X	Comparison of change scores between conditions
	• Travel behaviour • No. of trips • Transport mode (walking, cycling, e-cycling, car, bus, train) • Trip purpose	QStarz GPS and travel diary	X		X	X	Mean and SD
	• E-cycling behaviour and intensity: no. of journeys, duration, distance travelled, purpose of use	Bike odometer, Fitbit Charge 5 GPS watch, logbook		X			Mean and SD

^a^CRANK-P only, ^b^CRANK-B only

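### The only contamination check the protocol names is contact between participants, which does not measure whether controls e-cycled; use outside two observed weeks can be missed

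*Protocol article*

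**What the plan says.** The Control group section gives the check and its purpose together: "Participants will be asked to report any contact they have with other individuals in the study to ensure no contamination between conditions has occurred". It describes calls to controls at about weeks 4 and 8, which cover cancer treatment and support groups. It states no contact between T1 and T2. No question on e-bike use is mentioned.

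On routes to an e-bike outside the trial, the 3-month follow-up section describes a booklet for the e-bike arm: "This will include how to access the cycle2work scheme, information on community e-bike trial sessions, community e-bike loan availability and e-bike discounts".

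On measurement of e-cycling, the section on e-cycling behaviour and intensity says: "E-cycling behaviour will be measured during the intervention and follow-up period in the intervention group using a Fitbit Charge 5 watch". The logbook is the alternative to the watch, and the odometer is built into the trial's own bikes.

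Travel behaviour is recorded by GPS and a 7-day diary at baseline, "in the final week of the intervention and in the final week of the 3-month follow-up". In the diary, "For each journey, participants will be asked to report the travel mode, start and end time and start and end location". Table 3 lists the modes as "Transport mode (walking, cycling, e-cycling, car, bus, train", so e-cycling is separate from ordinary cycling. The Quantitative analysis section plans a "comparison of change scores between conditions for all outcome measures (except e-cycling during the intervention", so travel behaviour is collected in controls as well.

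**The concern.** In a waitlist trial of e-cycling, the contamination that matters for the comparison is e-cycling by controls before T2. The stated check asks about something else, and contact is neither necessary nor sufficient for that exposure. If the check is followed as written, a report of no contact could be taken as no contamination while some controls were riding.

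Two things are at stake. The first is a feasibility result: whether people who agreed to join an e-cycling trial, and who know they are on the waitlist, stay unexposed for about six months. That matters to the choice of control in a definitive trial. The second is the reading of the change-score differences offered as evidence of promise, since e-cycling in the control arm would tend to narrow them. An exposure history that nobody asked for cannot be recovered at the analysis.

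**Working it through.** The protocol states no contamination rate, so there is no figure to reproduce. The check is a side-by-side reading, followed by illustrative arithmetic.

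**What each source shows about e-cycling in controls**

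- Contact report (Control group): shows contact, not riding.
- Week 4 and 8 calls (Control group): stated topics do not include e-bikes.
- Watch, logbook, odometer (E-cycling behaviour and intensity): intervention arm only.
- Interviews (Feasibility and acceptability): all participants, but the stated focus is the intervention and the data collection.
- GPS and travel diary (Travel behaviour; Table 3): do show e-cycling in controls, for one week at the end of each period.
- Table 3: has no contamination outcome. Travel behaviour is summarised by mean and SD, which does not give the number of controls who e-cycled.

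**Share of time observed.** 1 of 12 intervention weeks = 8.3%; about the same for the 3-month follow-up.

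**Chance that the final-week window catches a control who rides in k of 12 weeks** (the riding patterns are assumptions)

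- Weeks scattered at random: k/12.
- One block of consecutive weeks placed at random: 12 − k + 1 possible positions, of which one includes week 12, so 1/(13 − k).
- Starts and continues to the end: 1.

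| k | Scattered | One random block | Starts and continues |
|---|---|---|---|
| 1 | 8% | 8% | 100% |
| 3 | 25% | 10% | 100% |
| 6 | 50% | 14% | 100% |
| 12 | 100% | 100% | 100% |

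**How likely any crossover is.** With 20 controls per trial (Sample size) and an assumed crossover probability c, the chance of at least one is 1 − (1 − c)^20: 64% for c = 5%, 88% for 10%, 99% for 20%. A finding of none therefore needs a measure that could have detected some.

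**Possible effect on the difference.** If m of 20 controls each gain a fraction f of the intervention effect, the difference shrinks by (m/20) × f.

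- f = 1: 10%, 20% and 30% for m = 2, 4 and 6.
- f = 0.25, for example riding in 3 of 12 weeks with effect proportional to use: 2.5%, 5% and 7.5%.

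The value f = 1 fits sustained riders, whom the diary would tend to show. The riders most likely to be missed have a smaller f.

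**The case against.** The strongest reply is that the trial already records e-cycling in controls. GPS and diary data are collected in both arms, e-cycling is its own mode, and anyone riding regularly at T1 or T2 would appear. This stands. A reader might infer that controls who cross over go undetected altogether; the Travel behaviour section and Table 3 do not support that.

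A reader might also infer a loss of 10% to 30% in the effect estimates. That does not follow either. It assumes that a crossing control gains the whole benefit of a programme with training, refresher sessions and a 12-week loan, and such a rider is not the one likely to be missed.

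Third, that the community schemes are open to controls is an inference. The 3-month follow-up section shows that such routes exist locally, but it gives no access conditions, and the booklet goes only to the e-bike arm.

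Fourth, the contact question has a legitimate use. The social media group and the study rides are real channels for leakage between arms, and independent use of a public scheme can be seen as background uptake under standard care. This justifies keeping the question, but not relying on it as evidence that controls did not ride.

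Finally, interview guides and visit forms may sit in a fuller protocol, so it cannot be said that the travel data will never be used for this purpose. What can be said is that the article states a specific check with a specific aim, and that the check measures something other than e-cycling by controls.

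**Conclusion.** The point holds in a limited form. The one check tied to contamination targets contact rather than e-cycling, and the data that do capture e-cycling in controls cover about one week in twelve and are not linked to contamination in the article. Controls who ride outside those weeks can be missed; regular riders would be seen.

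The size cannot be fixed from the documents. The detection chances, crossover rates and dilution figures all rest on assumed riding patterns and effects, and serve only as illustration. The consequence is modest: the primary outcomes are feasibility measures, the analysis is descriptive, and p-values are not considered. It still deserves correction, because whether waitlist controls remain unexposed is something this pilot is well placed to learn.

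**What to change.** - At T1 and at T2, ask every control whether they bought, borrowed, hired or rode an e-bike since the last assessment (yes/no, start date, approximate frequency).
- Report the number and percentage of controls with any e-bike use by T1 and by T2, with the number who answered, alongside e-cycling trips by arm from the existing diary and GPS data.
- Keep all participants in their randomised arm, and interpret the change-score differences in the light of that figure.
- Keep the contact question as a supplementary check on leakage between arms.
- Do not add the new question to the week 4 and 8 calls, where it may prompt uptake.

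The cost is one short item at two visits that already take place and one line in the results. The downside is recall over about three months instead of a shorter interval, which is small for a yes/no question about having used an e-bike.
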